## Abstract

**Background:**

Partial breast irradiation (PBI) is standard of care in low-risk breast cancer patients after breast-conserving surgery (BCS). Pre-operative PBI can result in tumor downstaging and more precise target definition possibly resulting in less treatment-related toxicity. This study aims to assess the pathologic complete response (pCR) rate one year after MR-guided single-dose pre-operative PBI in low-risk breast cancer patients.

**Methods:**

The ABLATIVE-2 trial is a multicenter prospective single-arm trial using single-dose ablative PBI in low-risk breast cancer patients. Patients ≥ 50 years with non-lobular invasive breast cancer ≤ 2 cm, grade 1 or 2, estrogen receptor-positive, HER2-negative, and tumor-negative sentinel node procedure are eligible. A total of 100 patients will be enrolled. PBI treatment planning will be performed using a radiotherapy planning CT and -MRI in treatment position. The treatment delivery will take place on a conventional or MR-guided linear accelerator. The prescribed radiotherapy dose is a single dose of 20 Gy to the tumor, and 15 Gy to the 2 cm of breast tissue surrounding the tumor. Follow-up MRIs, scheduled at baseline, 2 weeks, 3, 6, 9, and 12 months after PBI, are combined with liquid biopsies to identify biomarkers for pCR prediction. BCS will be performed 12 months after radiotherapy or after 6 months, if MRI does not show a radiologic complete response. The primary endpoint is the pCR rate after PBI. Secondary endpoints are radiologic response, toxicity, quality of life, cosmetic outcome, patient distress, oncological outcomes, and the evaluation of biomarkers in liquid biopsies and tumor tissue. Patients will be followed up to 10 years after radiation therapy.

**Discussion:**

This trial will investigate the pathological tumor response after pre-operative single-dose PBI after 12 months in patients with low-risk breast cancer. In comparison with previous trial outcomes, a longer interval between PBI and BCS of 12 months is expected to increase the pCR rate of 42% after 6–8 months. In addition, response monitoring using MRI and biomarkers will help to predict pCR. Accurate pCR prediction will allow omission of surgery in future patients.

**Trial registration:**

The trial was registered prospectively on April 28th 2022 at clinicaltrials.gov (NCT05350722).

## Background

Over the last decades, the introduction of breast cancer screening and the implementation of digital mammography and MRI have resulted in an increased incidence of early-stage breast cancer. The incidence will continue to increase due to the growth and aging of the population and the increasing prevalence of risk factors across the world [1, 2]. Additionally, by scaling up traditional treatment and imaging modalities, the global 5-year net survival is estimated to rise from 67.9% to 78.2% [3]. Both trends result in an ongoing increase in the absolute number of breast cancer patients, for example from 3.9 million in 2019 to an expected 5.0 million in 2030 in the United States [4]. At the same time, there is a shift towards personalized and less invasive therapies aiming to decrease treatment-associated toxicity and to improve cosmetic results and quality of life of patients without compromising oncological safety. The most applied standard treatment for early-stage breast cancer is breast-conserving surgery (BCS) followed by whole breast irradiation (WBI) [5, 6]. However, the majority of ipsilateral breast tumor recurrences (IBTR) occur at or in the vicinity of the primary tumor site [7]. Therefore, partial breast irradiation (PBI), in which only the tumor bed is irradiated, has recently become standard treatment for low-risk patients [8]. In general, patients are eligible for PBI when they meet the American Society of Radiation Oncology (ASTRO) or the European Society for Radiation Oncology (ESTRO) suitable criteria [9, 10].

Postoperative PBI leads to a smaller irradiated breast volume, reduced radiotherapy-associated toxicity, and similar 5-year (0.5% vs. 1.1%) and 10 year (3.7% vs. 2.5%) IBTR rates compared to WBI [11, 12]. Nevertheless, postoperative PBI remains challenging as delineation of the tumor bed can be difficult, due to distortion of the breast and postoperative seroma in the surgical cavity, resulting in unnecessarily large irradiated volumes. In contrast to postoperative tumor bed delineation, pre-operative tumor delineation allows more precise target delineation with less interobserver variation between radiation oncologists, and smaller irradiated volumes since the tumor is still in situ [13–16]. As a result, radiotherapy-associated toxicity could be reduced and quality of life improved. Additionally, pre-operative PBI allows a higher radiotherapy (RT) dose per fraction due to the smaller target volume, thereby allowing ultra-hypofractionation to ultimately one single dose, and reducing treatment burden.

Pre-operative external beam PBI has previously been investigated in patients with low-risk breast cancer [17–24]. These studies showed excellent oncological outcomes with local recurrence in 0–3% of the patients and overall survival of 97–100% after a follow-up of 21 to 60 months [19, 21, 23]. Acute and late toxicity was mild to moderate in the majority of patients [17, 19–23]. Cosmetic outcomes reported by both patients and physicians were good to excellent in respectively 78–100% and 89–100% of the patients [19–23]. In the ABLATIVE study (NCT02316561), which preceded the current study, pathologic complete response (pCR) was achieved in 42% of the patients at 6 to 8 months after single-dose ablative pre-operative PBI [21]. This was higher compared to other studies that evaluated pCR after single-dose pre-operative PBI, potentially due to the longer interval between RT and BCS [17, 18, 20, 25].

Response monitoring using MRI is standard clinical practice in patients treated with pre-operative systemic therapy [26, 27]. After pre-operative RT, data on radiologic response on MRI or other imaging are limited. Two studies showed that a radiologic complete response (rCR) on MRI had a positive predictive value (PPV) for pCR of 67–88% and negative predictive value (NPV) of 76–85% after pre-operative PBI [21, 28]. This means that a significant proportion of patients with rCR on MRI still have residual tumor in the surgical specimen. In the ABLATIVE trial, 67% of patients with rCR had a pCR and 33% had near pCR after 6 to 8 months [21]. Additionally, the prediction of pCR after pre-operative systemic therapy using liquid biopsies and biomarkers in tumor tissue, such as tumor-infiltrating lymphocytes (TILs), have been evaluated, and to a much lesser extent after pre-operative RT [21, 29–31]. The ABLATIVE trial showed presence of TILs pre-irradiation and 6 to 8 months post-irradiation [29]. No significant difference in the number of pre-irradiation TILs was observed in responders and non-responders treated with pre-operative PBI. Consequently, more data is needed to establish the predictive value of biomarkers and to develop prediction models for pathologic response in patients treated with pre-operative RT. If pCR can be more accurately predicted after pre-operative PBI in the future, surgery could be omitted in these low-risk patients. In future patients without a pCR, single-dose pre-operative PBI could replace multiple fractionated post-operative radiotherapy, and tumor downstaging could lead to excision of less healthy breast tissue.

The ABLATIVE-2 trial aims to assess the rate of pCR in low-risk breast cancer patients treated with MR-guided single-dose pre-operative PBI. In addition, radiologic response on MRI, toxicity, oncological outcomes, cosmetic outcomes, quality of life, liquid biopsies, and immune response markers in blood and tumor tissue will be evaluated before and after pre-operative PBI.

## Methods/design

### Study design

The ABLATIVE-2 trial is a Dutch multicenter, phase II, single-arm prospective study at the Radiotherapy Departments of the Amsterdam University Medical Centres (UMC) and Radboudumc in the Netherlands. Eligible patients are treated with MR-guided pre-operative PBI. BCS will be performed at 12 months post-PBI. Between RT and surgery, tumor response is monitored using MRI at 2 weeks, 3, 6, 9 and 12 months, and compared with the baseline MRI (before PBI). In case of tumor progression on MRI at any time or when residual tumor at 6 months is suspected, BCS is performed immediately (within two to four weeks). The primary objective of this study is to determine the rate of pCR one year after single-dose ablative RT and BCS in patients with early-stage breast cancer. The secondary objectives are to evaluate the radiologic response on MRI, radiotherapy- and surgery-induced toxicity, cosmetic outcome, and patients’ quality of life and distress. The oncological outcomes: local, regional, and distant relapse rates and overall survival will be assessed. Liquid biopsies and immune response markers in blood and tumor tissue pre- and post-RT will be evaluated. All tumor tissue and blood samples of patients will be preserved at the Amsterdam UMC Central Biobank, location Vrije Universiteit Medical Center (VUmc).

### Study population

Patients are eligible if they have histologically confirmed invasive breast cancer with low-risk characteristics according to the suitable criteria of the ASTRO guidelines for PBI [9, 10]. Low-risk criteria in this trial are women of 50 years or older with a cT1N0 non-lobular tumor, Bloom and Richardson grade 1 or 2, hormone receptor-positive, and HER2-negative. The inclusion and exclusion criteria are summarized in Table 1 [9].

**Table 1 Tab1:** Inclusion and exclusion criteria for the ABLATIVE-2 trial

Inclusion criteria	Exclusion Criteria
World Health Organization performance status 0–2	Legal incapacity
Females ≥ 50 years with a unifocal cT1N0 tumor	Breast cancer mutation gene carrier
Tumor histology as assessed on biopsy:	Distant metastasis
- Bloom-Richardson grade 1 or 2	Previous history of breast cancer or DCIS
- Non-lobular invasive histological type carcinoma	Another type of malignancy within 5 years before breast cancer diagnosis^a^
- Estrogen receptor positivity - HER2 receptor negativity	Signs of extensive ductal carcinoma in situ on histological biopsy or imaging
Tumor-negative sentinel node	MRI contra-indication
Adequate understanding of the Dutch language	Collagen synthesis disease
	Indication for treatment with (neo-)adjuvant chemotherapy
	Non-feasible dosimetric plan

^a^For patients with adequately treated carcinoma in situ of the cervix or basal cell carcinoma of the skin no specific time to the breast cancer diagnosis is required for inclusion. DCIS ductal carcinoma in situ

### Study outcomes

The primary endpoint is the rate of patients with pCR one year after single-dose pre-operative RT treatment. Secondary endpoints are the time to rCR on MRI and the correlation between radiologic and pathologic response. In addition, radiotherapy- and surgery-induced toxicity will be assessed according to the Common Toxicity Criteria Adverse Events version 5.0 [32]. Patient-reported outcome measures will be assessed using the European Organization for Research and Treatment of Cancer core-30 (EORTC-QLQ-C30) and breast cancer-specific (QLQ-BR23) quality of life questionnaires and the Hospital Anxiety and Depression Scale (HADS) questionnaire. Cosmetic outcome is assessed by the patient using the BREAST-Q questionnaire. The radiation oncologist rates the cosmetic outcome as excellent, good, fair, and poor, based on breast changes such as telangiectasia and fibrosis. Cosmetic evaluation is also performed objectively using imaging captured by the VECTRA XT 3D-imaging system (Canfueld Sci, New Jersey, USA). Oncological outcomes are assessed using local, regional and distant relapse rates, and disease-free and overall survival since RT. Additionally, liquid biopsies and radiotherapy-associated immune response markers in blood and pre- and post-RT tumor tissue are investigated. The time points for the evaluation of outcomes are displayed in Fig. 1.

**Fig. 1 Fig1:**
[figure not shown]
Overview of outcome measurements. Time points counted from radiotherapy treatment. Legend: w weeks, m months, y years. *questionnaires include evaluation of cosmetic outcomes and quality of life

### Procedures

In Fig. 2 an overview of all study procedures in the ABLATIVE-2 trial is shown. The dedicated breast surgeon or breast cancer nurse will inform the patient during consultation on the possibility of participation in a trial evaluating pre-operative single-dose RT with delayed surgery. If the patient is interested in trial participation, written study information is handed over and additional information is given by the physician-researcher. This is followed by a referral for pre-operative consultation with the dedicated breast radiation oncologist.

**Fig. 2 Fig2:**
[figure not shown]
Overview study design. *Additional consent required

#### Diagnostic workup

After informed consent, several procedures are required to confirm that the patient meets the eligibility criteria. First, a diagnostic MRI with perfusion and diffusion sequences in prone position is performed to exclude tumor multifocality or multicentricity and to assess tumor diameter. If no marker has been inserted in the tumor during the diagnostic biopsy, the radiologist will place an MRI-compatible marker in the tumor. Since pre-operative treatment will lead to tumor downstaging, a marker is mandatory for tumor localization during excision. After separate additional consent, extra tumor biopsies will be performed and stored in the Biobank. Secondly, the surgeon will perform a sentinel node procedure using technetium-99 m-nanocolloid, to rule out nodal involvement.

#### Treatment planning

Besides the standard radiotherapy planning CT in the treatment position, a planning MRI scan will be performed in treatment position. The gross tumor volume (GTV), which is the breast tumor on the diagnostic MRI, will be delineated on the planning MRI by a radiation oncologist specialized in breast cancer. GTV delineation is verified by a dedicated breast radiologist. To account for microscopic disease, the GTV is uniformly expanded by 2 cm to create the clinical target volume (CTV), while excluding the first 5 mm below the skin and the entire chest wall including the pectoral muscles, and not extending outside the breast tissue. For generating the planning target volumes (PTV), the GTV and CTV are expanded by 3 mm to obtain the planning target volumes PTV_GTV_ and PTV_CTV_, respectively. The PTV is a margin to account for patients’ movements during treatment and setup uncertainties.

For MR-guided radiotherapy, intensity modulated radiotherapy (IMRT) technique will be used on the MRIdian (ViewRay, USA) or Elekta Unity (Elekta, Sweden). On the conventional linac, IMRT or volumetric modulated arc therapy (VMAT) techniques will be used. In a single fraction, two RT dose levels are concomitantly prescribed: 15 Gy to the PTV_CTV_ and 20 Gy to the PTV_GTV_. Adequate target coverage is defined as a Dmean of the PTV_GTV and_ PTV_CTV_ of 99–101%, 98% or more of the PTVs receiving at least 95% of the prescribed dose and 2% or less of the PTVs receiving 107% of the prescribed dose, whilst respecting the organs at risk (OAR) doses (Table2). If optimal target volume cannot be achieved without exceeding the predefined dosimetrical constraints, the patient will be excluded from the study. In Fig. 3 an example of a single-dose PBI treatment plan is illustrated.

**Table 2 Tab2:** Dose constraints for organs at risk in the ABLATIVE-2 trial

Heart	V_2.8 Gy_ < 10%
	V_4.7 Gy_ < 5%
	D_mean_ ≤ 1.2 Gy
	V_16Gy_ < 15 cc
Lungs	D_mean_ ≤ 2.66 Gy
Ipsilateral lung	V_6.2 Gy_ < 10%
	V_12.4 Gy_ < 0.5 cc
Chest wall	D_20cc_ < 16 Gy
	V_20Gy_ < 1 cc
Skin	Dose as low as possible; aim for D_0_._1 cc_ < 12 Gy if this is not feasible aim for D_0_._1 cc_ < 16 Gy
Optional dose constraints	
Ipsilateral breast	D_mean_ < 5 Gy
	PTV_CTV < 25% of total ipsilateral breast volume
Contralateral breast	No constraint, dose as low as possible

**Fig. 3 Fig3:**
[figure not shown]
Dose distribution of single-dose ablative radiotherapy on MRIdian (Viewray, USA). Legend: The red isodose (20 Gy) represents the prescribed dose to the gross tumor volume (GTV). The green isodose (19 Gy) represents 95% of the prescribed dose to the GTV. The yellow isodose (15 Gy) represents the prescribed dose to the clinical target volume (CTV). The blue isodose (14.3 Gy) represents 95% of the prescribed dose to the CTV

#### Radiotherapy treatment delivery

The single-dose PBI will be delivered within three weeks following the planning MRI- and CT scan. On the conventional linacs and the MRIdian (ViewRay Inc., USA), MR-guided RT delivery will take place either with repeated breath-hold periods for patients with significant tumor movement or in free breathing when the tumor position is not affected by the breathing movement. On the Elekta Unity (Elekta, Sweden), treatment delivery will be performed using free-breathing. On both MR-linacs, online adaption of the treatment plan will be performed based on the MRI immediately before treatment delivery. Real-time MRI tumor tracking will be used on the MRIdian during the treatment procedure. On the conventional linacs, real-time position management and/or surface guidance will be used for patient tracking. The patient will fill out a questionnaire on comfort during the treatment procedure.

#### Follow-up after single-dose ablative treatment

Frequent clinical and radiological evaluation will be performed after single-dose PBI at 2 weeks, 3, 6, 9, and 12 months. Tumor response will be classified according to the ‘Response Evaluation Criteria in Solid Tumors’ guidelines [33]. Radiologic complete response on MRI is defined as the complete absence of pathologic contrast enhancement and complete absence of pathologic apparent diffusion coefficient reduction in the original tumor bed. Additionally, at baseline and during each follow-up consultation (i.e. at 2 weeks, 3, 6, 9, and 12 months) blood samples will be taken.

Patients with an indication for endocrine therapy will start this treatment following RT. The treating medical oncologist will monitor the endocrine treatment. If the surgical specimen shows any microscopic findings resulting in an indication for the start or change of adjuvant systemic therapy according to the Dutch national guidelines, patients will be treated accordingly [34].

#### Breast-conserving surgery

To assess the effect of RT on the breast tumor, BCS is performed at 12 months following RT. BCS will be performed ahead of time in case radiologic tumor progression (an increased size of contrast enhancement) is observed, or in case the MRI does not show rCR at 6 months following RT.

The surgical specimen is evaluated by a dedicated breast pathologist at the hospital where the surgery is performed. Viable tumor cells will be evaluated using hematoxylin and eosin staining and the activity of cytokeratin antibodies. Pathologic response will be categorized according to the European Society of Mastology (EUSOMA criteria).1. Complete pathologic response is defined as either no residual carcinoma or no residual invasive carcinoma but ductal carcinoma in situ (DCIS) may be present.2. Partial response to therapya. Near complete response is defined as minimal residual disease (<10% tumor cells)b. Evidence of response (10-50% tumor cells)c. >50% tumor cellularity remains evident with features of response present (e.g. fibrosis)3. No evidence of response

In addition, the proportion of patients with DCIS in the surgical specimen will be recorded. The surface of the excision specimen will be marked with Indian ink to evaluate surgical margins. Surgical margins will be described as minimal microscopic tumor-free margins of invasive and in situ carcinoma in millimeters (mm). This will always be performed in the direction of the nearest surgical margin. If tumor-positive margins are found, a radical re-excision needs to be performed.

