### Statistical analysis

Sample size calculation is performed based on the primary endpoint: the rate of pathologic complete response. We expect that 40% of our patients will achieve pathologic complete response 12 months after high-dose single fraction PBI. The sample size calculation is performed using the Wilson method for the calculation of different 95% confidence intervals (CI) for proposed sample sizes. A sample size of 100 patients would produce an acceptable 95% CI ranging from 30.9% to 49.8% while maintaining practical applicability.

The proportion of patients with pCR 12 months after RT will be evaluated and a 95% CI will be calculated. Regarding the secondary outcome, radiologic response, the negative and positive predictive value of radiologic response for pCR with 95% CIs will be calculated for all intervals between RT and BCS. Patient-reported and cosmetic outcomes will be analyzed in a linear mixed model for repeated measures. Radiation- and surgery-induced toxicity, local, regional and distant relapse rates, disease-free and overall survival will be reported using descriptive statistics. Kaplan–Meier method will be used to quantify disease-free and overall survival. The natural variability of the response markers will be evaluated for all accrued patients, exploring overlap in variance among the different response markers, and if applicable studying the reproducibility of the potential response markers.

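### Residual DCIS counts as pCR, and MRI predictive values are set only against that definition; a carcinoma-free reference should be pre-specified beside it

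*Protocol article*

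**What the plan says.** Under Study outcomes: "The primary endpoint is the rate of patients with pCR one year after single-dose pre-operative RT treatment". Under Breast-conserving surgery, category 1 of the EUSOMA classification reads: "Complete pathologic response is defined as either no residual carcinoma or no residual invasive carcinoma but ductal carcinoma in situ (DCIS) may be present". The same section adds "In addition, the proportion of patients with DCIS in the surgical specimen will be recorded" and, on margins, "Surgical margins will be described as minimal microscopic tumor-free margins of invasive and in situ carcinoma in millimeters".

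Radiologic complete response (rCR), defined under Follow-up after single-dose ablative treatment, requires "complete absence of pathologic contrast enhancement" and also no pathologic reduction of the apparent diffusion coefficient in the original tumor bed. It makes no exception for DCIS.

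Statistical analysis fixes the comparison of the two: "the negative and positive predictive value of radiologic response for pCR with 95% CIs will be calculated for all intervals between RT and BCS". No other pathological reference is named.

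The Discussion paragraph of the Abstract concludes: "Accurate pCR prediction will allow omission of surgery in future patients". The Background and the closing paragraph of the main Discussion make the same link, but conditionally. Table 1 excludes signs of extensive DCIS on biopsy or imaging; limited DCIS is not excluded.

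**The concern.** Category 1 pools two specimen states: no carcinoma at all, and in situ carcinoma without invasive carcinoma. For estimating the rate of EUSOMA pCR this raises no difficulty. It matters when the same category serves as the reference standard for MRI and the result is read as evidence on who might forgo excision, because then the reader wants to know whether any carcinoma was left.

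The test and the reference also treat DCIS differently. A patient with rCR and residual DCIS only is scored as a correct prediction. A patient whose residual DCIS enhances, and who therefore has no rCR, is scored as an MRI error. Against a carcinoma-free specimen both classifications reverse. Each case of the first kind makes the planned PPV higher than the PPV against the stricter reference. Each case of the second kind makes the planned NPV lower than the stricter NPV.

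The article has DCIS recorded, but as one proportion over specimens, not tied to pCR or rCR status. That proportion also includes specimens with DCIS next to invasive residual tumor, so by itself it cannot yield the stricter rate or predictive values. At stake is what the trial can say about omitting surgery, not the validity of its primary endpoint.

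**Working it through.** **Inputs from the article.** Expected pCR 40%, N = 100 and Wilson 95% CI 30.9% to 49.8% (Statistical analysis). Earlier PPV 67–88% and NPV 76–85%, with 67% the value in the preceding ABLATIVE trial (Background). The article does not say how the earlier studies handled DCIS, so these serve only as starting values.

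**Assumed input.** d = share of pCRs that are DCIS-only. The article gives no value, so 0%, 5%, 10% and 20% are shown. d is taken to be the same in patients with and without rCR.

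**Step 1: the plan's own figure.** Wilson interval with z = 1.96:
- centre = (p + z²/2n) / (1 + z²/n) = (0.40 + 0.0192) / 1.0384 = 0.4037
- half-width = z / (1 + z²/n) × √(p(1 − p)/n + z²/4n²) = 1.8875 × √(0.0024 + 0.000096) = 0.0943
- interval = 30.9% to 49.8%

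This matches the stated interval, so there is no arithmetic error in the plan.

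**Step 2: stricter rate.** Carcinoma-free rate = 40% × (1 − d), with the same Wilson interval on the resulting count out of 100.

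**Step 3: stricter PPV.** Among rCR patients, PPV × (1 − d) have a carcinoma-free specimen. For d = 10%: 67% × 0.90 = 60.3%.

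**Step 4: stricter NPV.** Among patients without rCR, 1 − NPV have pCR. Of these, a share d moves to the group with residual carcinoma, so stricter NPV = 1 − (1 − NPV)(1 − d). For d = 10% and NPV 76%: 1 − 0.24 × 0.90 = 78.4%.

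| d (assumed) | Rate (Wilson 95% CI) | PPV from 67% | PPV from 88% | NPV from 76% | NPV from 85% |
|---|---|---|---|---|---|
| 0% | 40% (30.9–49.8) | 67.0% | 88.0% | 76.0% | 85.0% |
| 5% | 38% (29.1–47.8) | 63.6% | 83.6% | 77.2% | 85.8% |
| 10% | 36% (27.3–45.8) | 60.3% | 79.2% | 78.4% | 86.5% |
| 20% | 32% (23.7–41.7) | 53.6% | 70.4% | 80.8% | 88.0% |

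**Step 5: sensitivity to the equal-share assumption.** If residual DCIS tends to enhance, DCIS-only cases gather among patients without rCR. The fall in PPV is then smaller than shown and the rise in NPV larger. In the limit where all of them lack rCR, PPV does not change. If residual DCIS tends not to enhance, the reverse holds. The effect on the overall rate depends only on the overall share.

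**The case against.** The strongest case against is that the plan is consistent with itself. Its stated aim and primary objective are to estimate the pCR rate, every patient is planned for surgery, and the predictive values are declared to be for pCR as defined. EUSOMA is a named classification. Both limbs of category 1 are written out, DCIS is recorded and extensive DCIS is excluded. A proportion of patients with DCIS presupposes a DCIS status for each patient, so the stricter figures can be derived later. A second cross-tabulation could also sit in the full protocol or the analysis plan, neither of which is shown. Finally, the Discussion calls prediction by MRI challenging and looks to blood, tissue and other radiological markers as well.

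Most of this stands, and it rules out a stronger reading. A reader might infer that the trial's goal is to omit surgery, and that its pCR rate and PPV therefore overstate how many patients could have avoided excision. The documents do not support that. Omission is a future prospect, no omission rule is tested, and an overstatement exists only if DCIS-only specimens occur. A reader might also take the margin text to show that such patients needed excision. The article says margins of in situ carcinoma are described and that tumor-positive margins lead to re-excision. It does not say what residual DCIS would mean for a patient spared surgery.

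The objection does not remove the point. The article fixes a single reference for PPV and NPV and, in the Abstract, links prediction of that reference to omission without qualification. That the data allow a stricter analysis later is a reason to name it now, before anyone knows which figures are more favourable.

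**Conclusion.** The point holds as a worthwhile improvement, not as an error in the primary endpoint, the sample size or the stated interval. If DCIS-only specimens occur, the planned pCR rate will exceed the carcinoma-free rate. The planned PPV will exceed its stricter counterpart to the extent that those specimens come from rCR patients, and the planned NPV will fall below its counterpart to the extent that they come from the others. Under the assumed shares the gap runs from nil to 8 percentage points on the rate (40% against 32%) and from nil to about 13 points on a PPV of 67% (against 54%). These figures illustrate and do not estimate: they rest on a DCIS-only share that the documents do not give and on that share being equal in both MRI groups.

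**What to change.** - Keep EUSOMA pCR as the primary endpoint, with N and its interval unchanged.
- Pre-specify one secondary endpoint: no residual invasive and no residual in situ carcinoma. Derive it from the DCIS status recorded for each specimen, and report it with a Wilson 95% CI on the same denominator as the primary rate.
- Report PPV and NPV of rCR, with 95% CIs, against both definitions.
- Wherever a report discusses omission of surgery, show the stricter rate and predictive values next to the EUSOMA ones.

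The cost is one more table, with no added reading, procedure or patients, provided DCIS status is kept per patient and not only as a total. The downside is that the stricter rate and PPV may be somewhat less favourable. If the full protocol or analysis plan already contains this breakdown, a sentence in the article pointing to it is enough.
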